**5.2 Echocardiography**

Echocardiographic assessment will be performed as part of the standard clinical care whilst the patients are still in hospital.

Images will be obtained using a 3.5 MHz transducer, at a depth of 12 to 20 cm in parasternal and apical views. Three cardiac cycles of the apical 4-, 3-, and 2-chamber views will be captured in 2D. Left ventricular volumes will be measured and the biplane Simpson’s rule will be applied.

Echocardiographic assessment of diastolic function (mitral E wave velocity/mitral annular velocity (E/E') ratio) and pulmonary congestion (PASP and IVC measurements) will be performed.

All echocardiographic data will be stored digitally and kept center for a centralized core lab reading. Two blinded expert operators will centrally assess data on a specific workstation.

**5.3 Measurement of tissue hypoxia and myocardial injury via troponin release**

Blood samples will be collected, centrifuged under standard conditions and cardiac troponin I will be determined in serum. Lactate concentration in arterial blood will be measured as an index of tissue hypoxia.

**5.4 Measurement of thyroid hormone levels**

Serum total T3, total T4 and TSH will be determined by standard immunoassays at different timepoints: baseline and at 24h, 48h, 72h, and every 3 days till termination of drug administration or end of follow-up. All samples for thyroid hormone measurements will be collected and analyzed at the end in order not to break the blindness of the trial. The coefficients of variation for each assay will be less than 5 percent. The cost of thyroid hormone measurements will be covered by the sponsor.

## 5.5 Recording and evaluation of clinical safety criteria

The following safety clinical criteria will be evaluated:

- Death
- Sudden cardiac death
- Cardiac Arrest
- Electromechanical dissociation
- Pulmonary Embolism
- Venous Thromboembolism
- Myocarditis
- Left Ventricular mural thrombus and/or embolism
- Congestive heart failure
- Cardiogenic shock and hypotension
- Septic shock
- New myocardial infarction
- Stroke
- Renal Failure
- Hepatic Failure
- Stress Ulcers
- Bleeding
- Thrombocytopenia
- Disseminated intravascular coagulation
- Ventricular fibrillation or Sustained ventricular tachycardia
- Rythm disturbances and serious bradycardia that require a pacemaker implantation
- [Paroxysmal supraventricular tachycardia](http://emedicine.medscape.com/article/156670-overview), [atrial flutter](http://emedicine.medscape.com/article/151210-overview), and [atrial fibrillation](http://emedicine.medscape.com/article/151066-overview)
- Vital signs (heart rate, blood pressure)

## 5.6 Recording and evaluation of adverse events

Individual adverse events (AE) will be evaluated by the investigators and they will be reported to the sponsor and Chief Investigator. This includes the evaluation of seriousness, causality and expectedness and any relationship between the investigational medicinal product(s) and/or concomitant therapy and the adverse event. Adverse events will be recorded during hospital stay and till the end of 30 days follow-up. A 24h telephone line will be available for all patients in order to communicate with a study investigator and report any adverse event during the follow up period if necessary.

## 5.7 Recording and evaluation of laboratory and instrumental safety criteria

A number of laboratory measurements will be performed in blood samples in order to evaluate disturbances in blood cells, renal dysfunction, hepatic dysfunction and dysfunction in glucose homeostasis.

The following parameters will be measured Haemoglobin, white blood cells, platelets, urea, creatinine, Glucose, CPK, LDH, AST, ALT, γ-GT, Total and Direct bilirubin, Albumin and total protein, INR, fibrinogen, d-dimer, Electrolytes (Na, K, Ca, phosphate, Mg), Troponin I, BNP, urine volume.

12-leads ECG will be performed every day during ICU stay and every 2 days during hospital stay to assess basal heart rate and cardiac rhythm.

Pulmonary function will be assessed by regular measurements of blood gases (pO2, pCO2, blood pH,lactate).

The course of *COVID-19* infection will be assessed by regular temperature monitoring, inflammatory indices (white blood cells, CRP, IL6, Procalcitonin, Ferritin, D-Dimers) and positivity for active replication of *COVID-19.*

**6 ENROLLMENT OF PATIENTS**

**Number of patients planned to be enrolled**

The primary end-point assessed in the present study will be the percentage of patients successfully weaned after 30 days of follow-up. According to reports that have been published in critically ill patients with COVID19 infection the percentage of patients successfully weaned after mechanical ventilation is low and approximately 15% (1,2). We assume that T3 treatment can increase successful weaning to 50% of patients which is a significant clinical improvement and is close to the mean percentage of successfully weaned sepsis patients (14). With these assumptions the sample size of 60 patients (that indicates 30 subjects for each group) will have **84**% power to detect the estimated difference between the two study groups. The criterion for significance (alpha) has been set at 0.05 and the test is 2-tailed.

***Figure 6.****Graph showingSample size estimation*

This study will start in ICU center of “ATTICO” University Hospital. We aim to include two more clinical sites in the trial one from Greece and one from Germany.

**7 WITHDRAWAL OF PATIENTS AND DEVIATION FROM THE PROTOCOL**

**Specification on criteria for withdrawal of patients: Patient and Investigator criteria**

Clinical follow-up will be performed for all patients randomized in the study even when they are withdrawn for any reason. If for any patient either the study treatment or observations were discontinued the reason will be recorded and documented in the CRF. Withdrawn subjects will be replaced and after the end of the study the number and reasons of withdrawn subjects will be reported both in treatment and placebo group.

Reason that a patient may discontinue participation in this clinical study are considered to constitute one of the following:

- Subject or relative withdrew informed consent
- Unsatisfactory adherence to study protocol or protocol violation (including drug dosage administered, and visit attendance)
- Appearance of clinical status that render the patient unsuitable to continue the study
- Adverse effects related to drug/placebo administration
- Major (cardiac and non-cardiac death, cardiac arrest, reinfarction) and minor (potentially life-threatening arrhythmias) adverse events during the period of drug/placebo administration
- Necessity of therapy with drugs interfering with T3 such as amiodarone or anti-thyroid drugs.

Analysis of data collected programmed upon completion of follow-up of the first 30 patients to eventually discontinue the study in the case of excess adverse events or mortality. In the case of occurrence of a major event, drug/placebo administration will be promptly stopped.

The subject may withdraw from the study at any time without explanation, without losing the right to future medical care. The participation of the subject may, at any moment, be terminated by the investigator, if considered appropriate.

**Any deviation from the protocol (to be classified as Major and Minor) will be accepted only in case of emergency and/or after agreement with the Sponsor.**

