**Sponsor statement:**

### The study will be conducted according to this protocol, the Good Clinical Practice (GCP), the ICH guidelines, local laws and obligations and the World Medical Association Declaration of Helsinki *(Appendix 1)*.

**2. BACKGROUND AND RATIONALE**

**Background**

**Introduction**

Covid-19 has caused a pandemic with increased mortality in the population particularly in aging people and patients with chronic disease. A number of infected patients require hospital care and severe cases are admitted to ICU (intensive care units) due to sepsis/septic shock. The mortality rate of patients requiring ICU treatment was reported to be between 81%-97% (1, 2).

Sepsis is a complex disorder that develops as deregulated host response to an infection and is associated with acute organ dysfunction and a high risk of death.

The world health assembly and WHO made sepsis a global health priority in 2017 and have adopted a resolution to improve the prevention , diagnosis and management of sepsis. 2.8 million deaths per year are attributable to sepsis(3).

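### Section 7 replaces withdrawn patients and lists death as a withdrawal reason; if replaced patients leave the analysed 30 per group, primary-endpoint failures are removed by outcome

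*Protocol*

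**What the plan says.** Section 7 (Withdrawal of patients and deviation from the protocol) sets the replacement rule: "Withdrawn subjects will be replaced and after the end of the study the number and reasons of withdrawn subjects will be reported". The reporting is to be done for each arm. The reasons for which a patient may discontinue participation include "Major (cardiac and non-cardiac death, cardiac arrest, reinfarction) and minor (potentially life-threatening arrhythmias) adverse events during the period of drug/placebo administration" and "Adverse effects related to drug/placebo administration". The same section opens with a commitment that points the other way: "Clinical follow-up will be performed for all patients randomized in the study even when they are withdrawn for any reason".

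Section 6 defines the outcome and the size: "The primary end-point assessed in the present study will be the percentage of patients successfully weaned after 30 days of follow-up", with a "sample size of 60 patients (that indicates 30 subjects for each group" and a stated power of 84% for 15% against 50% weaned at two-sided 0.05. The flow chart in section 10 shows 60 randomised and 30 + 30 followed. Section 9 treats each patient until successful weaning or the end of follow-up, at most 30 days. The Introduction in section 2 gives the expected severity: "The mortality rate of patients requiring ICU treatment was reported to be between 81%-97" per cent.

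**The concern.** Death is both a way to fail the primary endpoint and a listed reason for a replaceable withdrawal. Because treatment runs until weaning or day 30, a death before weaning nearly always falls in the treatment period that the list refers to. Given the mortality that the protocol itself cites, this would be the commonest kind of failure.

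If each such patient is replaced and the analysis is made on the resulting 30 per group, the denominator is chosen by outcome and the comparison is no longer between the groups as randomised. The weaning percentage would then describe mainly patients who did not die or suffer a listed event, and any difference between arms in such events would carry over into the primary result.

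**Working it through.** **Inputs from the protocol.** Placebo weaning 15%, T3 weaning 50%, 30 per group, two-sided alpha 0.05, stated power 84% (section 6); chi-square and Fisher's exact test for categorical data (section 14); ICU mortality 81% at the lower end (section 2).

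**Inputs that are assumptions.** The share *w* of each arm withdrawn before weaning, and the rule that those patients are replaced and not analysed. The protocol gives no withdrawal shares, so a range is shown.

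**Step 1: the plan's own figure.** Pooled normal approximation: mean rate (0.15 + 0.50)/2 = 0.325; z = [0.35 × √30 − 1.96 × √(2 × 0.325 × 0.675)] / √(0.15 × 0.85 + 0.50 × 0.50) = (1.917 − 1.298)/0.614 = 1.007, so power is 84.3%. Exact enumeration over both binomials gives 84.7% for the uncorrected chi-square test and 77.7% for Fisher's exact test. The stated 84% reproduces; the sample-size calculation is not the problem.

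**Step 2: analysed rate under replacement.** If a share *w* is withdrawn before weaning and replaced until 30 remain, the analysed weaning rate is p/(1 − w), and 30/(1 − w) patients must be randomised to fill the arm.

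**Step 3: equal withdrawal.** With p = 0.15 and w = 0.81: 0.15/0.19 = 79% in both arms. There is no bias between arms, but the percentage no longer describes the randomised patients. Leaving 60 would need 60/0.19 ≈ 316 randomised (about 158 per arm). The upper mortality figure, 97%, cannot be combined with 15% weaned before death, since the two exceed 100%.

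**Step 4: unequal withdrawal.** The last two columns give the exact probability of a significant result favouring T3, 30 analysed per arm.

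| True weaning, T3 / placebo | Assumed withdrawn, T3 / placebo | Analysed rates | Chi-square | Fisher |
|---|---|---|---|---|
| 15% / 15% | none replaced | 15% / 15% | 2.6% | 0.9% |
| 15% / 15% | 20% / 10% | 18.8% / 16.7% | 4.0% | 1.7% |
| 15% / 15% | 50% / 20% | 30% / 18.8% | 16.9% | 10.8% |
| 15% / 15% | 75% / 60% | 60% / 37.5% | about 43% | 32% |
| 12% / 15% | none replaced | 12% / 15% | 1.2% | 0.3% |
| 12% / 15% | 70% / 40% | 40% / 25% | 23.0% | 16.0% |
| 50% / 15% | 30% / 70% | 71.4% / 50% | 39.6% | 29.9% |

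For the 75% / 60% row: 0.15/0.25 = 60% and 0.15/0.40 = 37.5%. The last row shows the opposite direction: with more withdrawals on placebo, an effective drug loses power, from 84.7% to 39.6% by chi-square.

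**Step 5: the other reading.** If replaced patients stay in the analysis, none of the bias above arises. But each replacement adds a randomised patient, so the total exceeds the 60 randomised in the section 10 flow chart and the 30 per group in section 6. One of these statements has to give way.

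**The case against.** No sentence in the protocol says that withdrawn patients leave the primary analysis. Section 7 keeps them in follow-up, so their 30-day status should be known, and the choice of analysis sets may stand in a statistical analysis plan that is not shown. Withdrawals are to be reported by arm, mortality is reviewed after 15 and 30 patients, and survival is compared by log-rank test (section 14). The list says a patient *may* discontinue, and a patient withdrawn for an arrhythmia or for amiodarone could still be weaned, so not every withdrawal removes a failure. Nor does the text say that a replacement enters the same arm. Finally, about 90 patients are to be screened and 60 randomised, which cannot accommodate replacing every death; loose drafting is the likelier explanation than an intention to select on outcome.

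Most of this stands, and it is why the point is conditional. It does not remove it. Replacement is an enrolment rule that the protocol itself fixes, so it is not a detail left to an analysis plan. The safeguards in section 14 do not define the denominator of the primary endpoint, and its missing-data text, including the comparison of full-set with complete-case results, concerns missing values and does not say how deaths or withdrawals count.

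A reader might go further and infer that the rule will make a harmful drug look effective. The documents do not support that: it requires exclusion from the analysis and clearly more withdrawal on T3. A reader might also point to atrial fibrillation in the ThyRepair table in section 9 (19% on T3, 7.7% on placebo) together with the listed reason "Necessity of therapy with drugs interfering with T3 such as amiodarone or anti-thyroid drugs". Those figures rest on 16 and 17 patients with p = 0.25, and nothing says that these patients received amiodarone. They do not show that withdrawal would be unequal.

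**Conclusion.** The point holds in conditional form and needs correcting before the trial is analysed. The text makes death a replaceable withdrawal while fixing 30 per group, and under either reading something is wrong: excluding replaced patients selects the analysed groups on outcome, and including them contradicts the planned 60.

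Under exclusion, the size depends wholly on withdrawal shares that the protocol does not give. A modest imbalance moves the false-positive rate in favour of T3 little; a 15-point imbalance at high event rates makes it many times the nominal value. Even in that case (75% against 60%) a significant result is not the usual outcome: a typical 18/30 against 11/30 gives p = 0.07 by chi-square and 0.12 by Fisher. The direction follows whichever arm has more withdrawals, so the rule could also hide a real benefit.

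**What to change.** - Delete the replacement sentence in section 7. Alternatively, state that replacements never substitute for randomised patients in the analysis, and change the totals in sections 6 and 10 to match.
- Separate stopping study drug from leaving follow-up, and do not class death as a withdrawal.
- State that the primary analysis includes every randomised patient as allocated, with death before successful weaning counted as not weaned and patients off study drug counted by their actual 30-day status.
- Reconcile sections 6, 7 and 10 on the number randomised and analysed.

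The section 7 rules on when study drug is stopped are left unchanged; only the classification and counting of patients is affected.

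The cost is a wording amendment. Follow-up of withdrawn patients is already planned, no extra patients are needed, and with all 60 counted the power at 15% against 50% remains 84.7% by chi-square or 77.7% by Fisher.

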**Assessment of weaning from cardiorespiratory support**

- Successful weaning is defined as no requirement for ventilatory support after extubation (mechanical support) or support from ECMO for 48 hours. The primary objective will be measured as percentage of patients successfully weaned after 30 days of follow-up. The percentage of patients weaned at 20 days post-intubation will be a relevant secondary endpoint.

The ***secondary objectives*** of the study are:

1. **Assessment of hemodynamic status**

Hemodynamic status will be assessed by continuous blood pressure measurements (systolic, diastolic and mean BP) and the use of inotropic and vasoactive drugs.

1. **Assessment of pulmonary function**

Pulmonary function will be assessed by arterial measurement of blood gases, Horowitz-Index (pO2/FiO2) and lactate.

1. **Assessment of hepatic and renal function**

Hepatic and renal function will be assessed by laboratory measurements in blood and urine volume

1. **Assessment of cardiac function**

Echocardiographic assessment of systolic and diastolic function will be performed. Measurements of cardiac troponin-I will be used to assess myocardial injury

1. **Assessment of the course of** *COVID-19* **infection**

COVID-19infection will be assessed by inflammatory indices and their course (daily changes and absolute values) in blood (IL6, Procalcitonin, D-Dimers, Ferritin and CRP), temperature monitoring and time needed for the patient to become negative in COVID-19.

1. **Assessment of clinical outcome and safety**

Major events (*death, cardiac Arrest, electromechanical dissociation, pulmonary embolism, new myocardial infarction, stroke, pulmonary edema, cardiogenic shock and hypotension, septic shock, pulmonary embolism, serious bleeding*) and minor (*myocarditis, Venous Thromboembolism, left Ventricular mural thrombus, renal failure, hepatic failure, stress ulcers, minor bleeding,* [*paroxysmal supraventricular tachycardia*](http://emedicine.medscape.com/article/156670-overview)*and*[*atrial fibrillation*](http://emedicine.medscape.com/article/151066-overview)*, rythm disturbances*) will be recorded during the follow up period.

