### Maximum duration of treatment of a subject

Each subject will be treated until successful weaning or end of follow up. The maximum treatment duration of a subject may reach 30 days.

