## *Proposed Storage conditions:* Store under 2-8^o^C.

**10.** **FLOW-CHART OF THE STUDY**

**General schedule for Patient and Investigator**

Patients with COVID19 pneumonia on mechanical ventilation or ECMO, n=90

Follow-up for 1 month, n=30

Follow-up for 1 month, n=30

Placebo group, n=30

T3 group, n=30

Randomisation 1:1, n=60

Assessment of eligibility, n=70

Signed inform consent, n=60

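### Withdrawn patients are replaced without exception and on-drug death is a listed reason to discontinue, so a failure on the primary endpoint can trigger replacement

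*Protocol*

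**What the plan says.** The replacement rule is in Protocol section 7: "Withdrawn subjects will be replaced and after the end of the study the number and reasons of withdrawn subjects will be reported". It carries no exception by reason.

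The same section then introduces a list with "Reason that a patient may discontinue participation in this clinical study are considered to constitute one of the following". One item reads "Major (cardiac and non-cardiac death, cardiac arrest, reinfarction) and minor (potentially life-threatening arrhythmias) adverse events during the period of drug/placebo administration". A later sentence adds "In the case of occurrence of a major event, drug/placebo administration will be promptly stopped".

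Section 7 also says "Clinical follow-up will be performed for all patients randomized in the study even when they are withdrawn for any reason".

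Two other places fix what an on-drug death means for the endpoint. Section 9 (Maximum duration of treatment of a subject) says "Each subject will be treated until successful weaning or end of follow up". Section 3 says "The primary objective will be measured as percentage of patients successfully weaned after 30 days of follow-up", and defines success as 48 hours free of ventilatory or ECMO support.

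The flow chart in section 10 shows "Randomisation 1:1, n=60", then 30 patients per arm in follow-up. Replaced patients do not appear in it.

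**The concern.** Replacement is harmless when the reason for leaving has nothing to do with the outcome, for example a patient who was never dosed. Here one of the listed reasons is an outcome. Drug stops at successful weaning, so a patient who dies on drug has not been weaned. For deaths, the trigger picks out only failures.

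The consequence depends on a choice the protocol leaves open:

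- **Replaced patients stay in the analysis.** The weaning rates remain unbiased. The cost is a total above the planned 60 that grows with mortality.
- **Replacements stand in for them.** Failures leave the denominator and both weaning rates rise. The arm with more replaced deaths rises more, so a drug that kills more patients could look better on weaning.

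Deaths are likely to be common in this population. Section 2 cites ICU mortality of 81% to 97%, and section 6 assumes only 15% weaned on placebo.

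**Working it through.** **The plan's own figure.** Section 6 gives 30 per arm, 15% v 50% weaned, two-sided alpha 0.05 and 84% power. With the pooled variance under the null (mean rate 0.325):

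- critical difference = 1.96 × √(2 × 0.325 × 0.675 / 30) = 0.237
- standard error under the alternative = √((0.15 × 0.85 + 0.50 × 0.50) / 30) = 0.112
- power = Φ((0.350 − 0.237) / 0.112) = Φ(1.007) = 84.3%

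The stated 84% is correct for 60 patients with nobody replaced.

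**Effect of replacing and leaving out deaths, no true effect on weaning.** The protocol gives neither an on-drug death rate nor a share of deaths replaced, so both are assumed. Let p be true weaning, m the proportion dying on drug, and r the share of those deaths replaced and left out. The apparent weaning rate is p / (1 − r·m). Take p = 0.15 in both arms and m = 0.50 on placebo. False-positive chances are exact enumerations of the uncorrected chi-square test at two-sided 0.05, 30 retained per arm, counting only rejections in favour of T3.

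| r | m, placebo v T3 | Apparent weaning, placebo v T3 | False positive for T3 |
|---|---|---|---|
| 0 | any | 0.150 v 0.150 | 2.65% |
| 1 | 0.50 v 0.60 | 0.15/0.50 = 0.300 v 0.15/0.40 = 0.375 | 8.5% |
| 1 | 0.50 v 0.65 | 0.300 v 0.15/0.35 = 0.429 | 17.2% |
| 0.5 | 0.50 v 0.60 | 0.15/0.75 = 0.200 v 0.15/0.70 = 0.214 | 3.3% |
| 0.5 | 0.50 v 0.65 | 0.200 v 0.15/0.675 = 0.222 | 3.9% |
| 1 | equal, 0.30 to 0.65 | equal | 2.4% to 2.5% |

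Section 14 also names Fisher's exact test. With it, the baseline is 0.9% and the two r = 1 cases give 5.3% and 11.4%. The direction is the same and the levels are lower.

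**Effect under the planned rates.** Suppose a share d of the unweaned patients in each arm die on drug and are replaced and left out. The apparent rate is p / (1 − d(1 − p)).

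| d | Placebo (true 15%) | T3 (true 50%) | Difference (true 35 points) |
|---|---|---|---|
| 0.25 | 0.15/0.7875 = 19.0% | 0.50/0.875 = 57.1% | 38.1 |
| 0.50 | 0.15/0.575 = 26.1% | 0.50/0.75 = 66.7% | 40.6 |
| 0.75 | 0.15/0.3625 = 41.4% | 0.50/0.625 = 80.0% | 38.6 |

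The difference moves by 3 to 6 points. The rates themselves move much more, and neither describes the patients who were randomised.

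**The case against.** The strongest reply is that the harm depends on the analysis set, which a statistical analysis plan normally defines and which is not at hand. Silence about where replaced patients are counted is therefore not in itself a fault. Several parts of the protocol also point to the harmless reading:

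- Follow-up of every randomised patient after withdrawal has little purpose if those patients leave the analysis.
- The stop sentence in section 7 concerns drug administration, so the list could be read as mainly about stopping drug.
- Mortality is an outcome in section 3 and is reviewed at the interim analyses in section 14, so dead patients are kept for those purposes.
- Section 11 screens about 90 to enrol 60. Replacing all deaths at 50% v 60% would need 30/0.50 + 30/0.40 = 135 randomised, which is not provided for.

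The size of the bias also rests on assumed inputs. The 8.5% and 17.2% figures need every death replaced and left out, and mortality 10 or 15 points higher on T3. Holding 30 retained per arm is a simplification, because blinded sequential allocation cannot replace within an arm. The bias can also run against T3: if a quarter of T3 failures and half of placebo failures are replaced, chi-square power falls to 69.8%. Cardiac arrest and reinfarction are not failures in themselves, since such a patient may still be weaned.

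These points stand as limits on the size and the likelihood of harm. They do not rescue the rule. Follow-up makes an analysis of all randomised patients possible but does not commit to one. The replacement instruction is also carried out at the sites during the trial, and a later analysis plan cannot undo enrolment that deaths have triggered.

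**Conclusion.** The concern holds and should be fixed. As written, section 7 lets an on-drug death, which is always a primary-endpoint failure, trigger replacement. That much is certain from the text for death only.

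Bias follows only if replacements stand in for the patients they replace. On that reading, and on the assumed inputs, the chance of a false positive for T3 ranges from no inflation (equal mortality), through 3.3% to 3.9% (half of deaths replaced), to 8.5% to 17.2% (all replaced, higher mortality on T3). On the other reading the weaning rates are sound and the defect is a sample size with no upper limit. Confidence is medium, because the intended reading is unknown. The stated power is not in error.

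**What to change.** Amend section 7 to say that:

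1. Stopping study drug is not withdrawal from the study.
2. Patients with a major event, including death, are not replaced.
3. Those patients count in the primary analysis in their randomised arm, as not weaned if they die on support.

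A smaller clarification belongs with this: say whether the major event that stops drug means the short list in section 7, or name the list the clinical team intends, since section 3 gives a longer one.

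The cost is protocol wording. No patients or procedures are added. With no replacement and all 60 randomised patients analysed, the planned 84% power is kept.
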